### 8.3 Recording and documentation of complications

Complications are recorded over a period of 90 days after inclusion in the study. In case of doubt, the study outpatient clinic should be contacted by telephone. In case of death, the

cause of death should be documented. Unexpected, previously unknown complications for which a causal relationship with the recommended measures cannot be ruled out will be reported to the study participants within one week.

All complications will be documented in the patient's chart and later recorded in the CRF by the SUPPORT study nurse.

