## 1.3 Summary

*Staphylococcus aureus* bacteremias (SAB) are major contributors to morbidity, mortality, and consequently healthcare costs (1,2). The SAB incidence in the Western world is approximately 26 per 100,000 population (3). About 2/3 of these infections are nosocomial-primarily catheter-associated-and about 1/3 are ambulatory-acquired (4-6). The 30-day mortality for nosocomial SAB was reported to be 22% in one study and 26% for ambulatory-acquired (4). Initial unpublished data from the AlertsNet project conducted at Jena University Hospital show a hospital mortality rate of 25%. Adequate treatment of SAB is nontrivial and includes proper choice and duration of antimicrobial therapy, infectious focus, and search for septic metastases and exclusion of infective endocarditis (1, 7). Data from nonrandomized and retrospective studies demonstrate that consultative co-management by clinical infectious disease specialists results in significantly improved survival, shorter hospital stays, and lower rates of complications, as well as reduced overall antibiotic use (8-17).

This is countered by the fact that a significant number of patients are treated in small and medium-sized hospitals. Due to the current shortage of clinical infectiologists, these cannot be cared for directly by one. In Thuringia, with more than 20,000 hospital beds, there are currently only 3 infectious disease specialist working in inpatient services. The requested cluster-randomized controlled cross-over SUPPORT study aims to test whether a telephone consultation by a clinical infectious disease specialist increases the survival of patients with SAB in Thuringia.

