#### 10.3.2.5 Infection focus

- Intrathoracic infection
- Urogenital/renal infections
- Infection of the central nervous system
- Bone and joint infections
- Infections of the cardiovascular system

- 566 -HNO/oropharyngeal infections
- 567 -Intraabdominal infections
- 568 -Skin and soft tissue infections
- 569 -Postoperative wound infections
- 570 -Flexure tube as suspected source of infection
  
- 571 10.3.2.6 Characteristics of blood culture
- 572 -Date of blood culture collection
- 573 -Location of blood culture collection
- 574 -Presence of foreign bodies or prostheses
- 575 -Further positive blood cultures
- 576 -Detection of other bacteria
  
- 577 10.3.2.7 Presence of SIRS criteria
  
- 578 10.3.2.8 Organ dysfunction within 7 days of 1st positive blood culture.
- 579 -Acute encephalopathy
- 580 -Thrombocytopenia
- 581 -Arterial hypoxemia
- 582 -Renal dysfunction
- 583 -Metabolic acidosis
  
- 584 10.3.2.9 Septic shock within 7 days after 1. positive blood culture.
  
- 585 10.3.2.10 Severity of SAB
- 586 -uncomplicated
- 587 -complicated
  
- 588 10.3.2.11 PITT score on the day of blood culture collection (24).
  
- 589 10.3.2.12 Charlson comorbidity index (23)
  
- 590 10.3.2.13 Recommended measures/implementation of the recommended measures
- 591 -Time
- 592 -Follow-up blood cultures
- 593 -Focus remediation
- 594 -Transesophageal echocardiography
- 595 -other proposed measures
  
- 596 10.3.2.14 Laboratory values on the day of the positive blood culture
- 597 - Creatinine
- 598 -Creatinine Clearance
- 599 -Bilirubin
- 600 -Lactate
- 601 -CRP
- 602 -PCT
- 603 -ALAT
- 604 -ASAT
- 605 -AP
- 606 -leukocytes
- 607 -platelets
- 608 -neutrophil granulocytes
- 609 -Ferritin

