#### 10.3.2.15 Patient status at hospital discharge

- ICD 10 Main diagnosis
- Place of discharge
- Mortality date
- Discharge date
- ITS stay during hospitalization.
- Complications
- Progression of the SAB

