#### 10.3.2.18 90 days follow up

- Successful contact
- Recent hospitalization and, if applicable, reason for admission
- Death of the patient
- new clinical complaints

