#### 10.3.2.19 Antimicrobial therapy since 1st positive blood culture until discharge/transfer.

- • Drug
- Application type
- Application duration

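### Section 8.3 promises 90 days of complication recording, but the post-discharge forms have no complication or antibiotic item, so later complications would be captured incompletely

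*Protocol*

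**What the plan says.** **The promise.** Protocol section 8.3: "Complications are recorded over a period of 90 days after inclusion in the study". The route follows in the same section: "All complications will be documented in the patient's chart and later recorded in the CRF by the SUPPORT study nurse". The synopsis (1.4) names safety relative to standard care, beside 30-day mortality, in the primary objective.

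**The CRF content (10.3.2).**
- Complications are one item in the block headed "Patient status at hospital discharge" (10.3.2.15).
- The itemised checklist follows directly as its own section (10.3.2.16). It names procedure-related events, kidney failure on vancomycin or aminoglycosides, liver failure on flucloxacillin or rifampicin, antibiotic allergy, *C. difficile* enteritis and a catch-all. It states no time window.
- The day-30 and day-90 forms (10.3.2.17 and 10.3.2.18) hold four items each: whether contact succeeded, rehospitalisation with its reason, death, and, in the wording of the day-90 form, "new clinical complaints".
- Drug exposure has an explicit end: "Antimicrobial therapy since 1st positive blood culture until discharge/transfer" (10.3.2.19).

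**The follow-up calls (7.7).** Their stated purpose is survival and recurrence to day 90. If the patient cannot be reached, the primary care physician or the study centre is asked. No visits are planned.

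**The concern.** A 90-day window is only as good as the instrument that covers it. After discharge the patient leaves the chart on which section 8.3 relies, and the telephone call becomes the trial's only active contact. That call is not set up to ask about complications or about antibiotics still being taken.

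This matters most for the drug-related items on the checklist, which can arise or be recognised after the patient has gone home or been transferred. Because exposure recording stops at discharge or transfer, a later event cannot be linked to a recorded drug.

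At stake is the safety half of the synopsis objective. Even a descriptive table of complications by arm needs a window that is the same for everyone and known to the reader. If capture in practice follows the inpatient stay, the window depends on a quantity that arises after randomisation and that the consultation might influence. Data not collected at the call cannot be recovered at analysis.

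**Working it through.** There is no figure of the plan to reproduce, because the point concerns a collection window. The check sets the sections side by side.

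1. **Required window.** Section 8.3 gives 90 days, counted from inclusion.
2. **Source up to discharge.** Sections 8.3, 10.3.1 and 10.3.2 all give the site's records, transcribed by the study nurse. The discharge block has a complication item and the checklist stands beside it. In-hospital complications are covered.
3. **Source from discharge to day 90.** The candidates are:
   - *Site chart.* It need not contain events treated by a primary care physician or in another facility.
   - *Day-30 and day-90 forms.* They have no complication item, no checklist and no drug item.
   - *Antimicrobial therapy record.* It is closed at discharge or transfer by its own heading.
   - *Checklist 10.3.2.16.* No cut-off is stated, so it may be filled in later, but no form or contact is assigned to prompt it.
4. **Is the omission an accident of the text?** The amendment that adds the 18-month call lists the content of the 30- and 90-day follow-up again and gives the same four items. The short list is what the protocol intends.
5. **What the calls do catch.** A complication that leads to readmission appears through the reason for admission. A fatal one appears as a death, for which 8.3 also wants the cause. A symptomatic one may appear as a new complaint. One managed on an outpatient basis, or not recognised by the patient as a complication, has no prompt. A recorded complaint does not name a drug or map to a checklist item.
6. **Consequence for a comparison.** Suppose that capture did stop at discharge and that the complication hazard were constant and equal in both arms. Expected counts would be proportional to mean observed days, so the ratio of counts would equal the ratio of mean observed days. The rate per observed day would be the same in both arms. A distortion of counts or risks therefore requires observed time to differ between arms. The protocol gives no length of stay by arm and no complication rate, so no value can be entered.

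A minor mismatch should be settled at the same time: 8.3 counts its 90 days from inclusion, whereas 7.7 times the calls from diagnosis.

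**The case against.** The strongest reply is that the protocol nowhere limits complications to the inpatient stay. The checklist is a separate section without a cut-off, and the authors did write a cut-off where they wanted one, for antimicrobial therapy. Read with 8.3, the checklist could be meant to run to day 90. Section 11.1 also leaves procedures and time windows to a study manual that is not available here. This stands as far as it goes: a discharge limit on the checklist is an inference, not stated text. It does not supply a means of collection, since the protocol's own list of follow-up items lacks one.

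Second, the calls capture part of what happens later, and 8.3 offers a telephone contact for doubtful cases. This also stands, so capture is incomplete rather than absent. Nothing in the documents says that an empty record is counted as no complication.

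Third, no between-arm safety analysis is specified. Sections 3.1, 3.2 and 9.1 contain no safety endpoint, and 8.2 defines complications by their relation to measures recommended in the consultation, which control patients do not receive. This limits the weight of the point. It does not remove the safety objective in the synopsis or the 90-day promise in 8.3.

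A reader might go further and infer that the consultation arm will look safer because its patients leave hospital sooner. Section 1.3 does cite "significantly improved survival, shorter hospital stays, and lower rates of complications". That statement rests on nonrandomised and retrospective studies of specialist co-management, and the protocol states no expected stay under telephone consultation. Section 2.3 links consultation to more echocardiography and adequate treatment duration, which could lengthen a stay, and a difference in survival would also alter observed time. The direction is therefore open.

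**Conclusion.** The point holds as an internal mismatch between 8.3 and 10.3.2. A 90-day complication record is promised, the only stated route is the site chart, no follow-up form carries a complication or antibiotic item, and drug exposure ends at discharge or transfer. Followed as written, the plan yields incomplete data on complications after discharge, most clearly for drug-related events.

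Unequal observation between the arms is a possible consequence if length of stay or survival differs. Its direction and size cannot be derived from the documents. Any numerical bias would rest on invented stays, and a constant hazard would fit poorly the checklist items that are tied to a single procedure.

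The primary mortality endpoint is not affected. The matter should be corrected because safety is in the synopsis objective and the missing information cannot be rebuilt later.

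**What to change.** Reconcile 8.3 with 10.3.2 in one of two ways.

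- **Keep the 90-day window.** Add three things to the day-30 and day-90 call forms, identically in both arms: the 10.3.2.16 checklist, the date of each complication, and antimicrobial use since the last contact. Put the same questions to the fallback informants already named in 7.7. State whether the 90 days run from inclusion or from diagnosis.
- **Or narrow the claim.** Restate the outcome in 8.3 as in-hospital complications, and give 10.3.2.16 the matching time window.

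The first option needs a change to the CRF and the call script and a few more minutes on calls already scheduled, with no extra visits or tests. Its drawback is that complications reported by telephone are less precise than chart entries, so the source of each report should be recorded. The second costs only wording, but gives up safety information after discharge.

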## 9 Biometrics

### 9.1 Endpoints

The primary endpoint of the study is 30-day all-cause mortality of patients starting from the time of SAB diagnosis.

The secondary endpoints are:

- Fulfillment of 6 of the defined quality indicators (yes/no).
- 90-day all-cause mortality starting from the time of SAB diagnosis.
- 90-day recurrence rate starting from the time of SAB diagnosis.
- Progression of SAB to sepsis/septic shock within the 90-day period (based on time of SAB diagnosis) (yes/no).
- Presence/development of septic metastases (abscesses, spondylodiscitis, osteomyelitis, endocarditis, etc.) within the 90 days (based on the date of SAB diagnosis) (yes/no).

Other parameters recorded:

Patient demographic parameters, Charlson comorbidity index (23). Infection focus, SIRS severity on admission/diagnosis, sensitivity to methicillin, antibiotic therapy performed, Pitt bacteremia score (24), cause of infection, primary site of *S. aureus* infection.

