### 2.3 Justification of the treatment and examination procedures

Data from nonrandomized and retrospective studies demonstrate that the inclusion of a clinical infectious disease specialist significantly improves the treatment and survival of SAB patients. Patients seen in consultation by an infectious disease specialist had higher rates of echocardiography, adequate duration of antibiotic therapy, and subsequently improved 30-day survival despite having more initial risk factors (8,9,17). A separate meta-analysis of 16 studies demonstrated that infectious disease consults can lead to a halving of SAB mortality (13% vs. 27%) (22). A recent study also demonstrated that adherence to an evidence-based bundle of measures improves the management of patients with SAB and reduces 14- and 30-day mortality (11). In contrast, a significant number of patients are treated in small and medium-sized hospitals and, because of the current shortage of clinical infectious disease specialists, cannot be directly managed by one. In Thuringia, with more than 20,000 hospital beds, there are currently only 3 clinical infectious disease specialist working in inpatient services.

The study aims to assess the extent to which non-requested telephone consultations in non-university hospitals in Thuringia significantly improve survival of patients with *Staphylococcus aureus* bacteremia. An overview of the procedure in the therapy arms is given in **section 7.1**. It is estimated that approximately 250 patients per year can be included in the study. If the study objectives can be confirmed by the results, it is conceivable that infectious disease telephone consults will be defined as the standard of care for all patients with SAB.

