### 3.2 Secondary endpoints

The secondary endpoints of the SUPPORT study are:

- Fulfillment of the 6 defined quality indicators
- 90-day all-cause mortality
- 90-day recurrence rate
- Antibiotic therapy performed
- Progression of SAB to sepsis/septic shock over a 90-day period.
- Development of septic metastases over a period of 90 days

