## 385 7.7 Follow-up surveys

386 The survival of the patients and the recurrence rate will be recorded up to 90 days after  
387 diagnosis of SAB. For this purpose, the patients or, if they are not available, the primary care  
388 physician or the study centers will be interviewed by telephone 30 and 90 days after  
389 diagnosis. Patient visits are not planned.

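### The septic-metastasis endpoint is worded two ways, one of which counts foci already present at diagnosis, and neither it nor the sepsis endpoint is specifically captured over its stated 90 days

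*Protocol*

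**What the plan says.** **Metastases.** Section 9.1 lists "Presence/development of septic metastases (abscesses, spondylodiscitis, osteomyelitis, endocarditis, etc.) within the 90 days", counted from SAB diagnosis and scored yes/no. Section 3.2 lists "Development of septic metastases over a period of 90 days", and the synopsis also names development only.

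**Sepsis.** Section 9.1 lists "Progression of SAB to sepsis/septic shock within the 90-day period (based on time of SAB diagnosis) (yes/no"; section 3.2 and the synopsis also speak of progression.

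**Data collection.** Section 10.3.2 sets out what goes into the CRF:
- item 10.3.2.8: "Organ dysfunction within 7 days of 1st positive blood culture";
- item 10.3.2.9: "Septic shock within 7 days after 1. positive blood culture";
- item 10.3.2.15, status at hospital discharge: "Progression of the SAB";
- items 10.3.2.17 and 10.3.2.18, the 30- and 90-day forms: contact made, hospitalization with its reason, death, new complaints.

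Section 7.7 describes the purpose of the calls: "The survival of the patients and the recurrence rate will be recorded up to 90 days after" diagnosis.

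**Work-up.** Section 7.5 gives transesophageal echocardiography (TEE) as an example of an examination recommended in the consult. Item 10.3.2.13 lists TEE, follow-up blood cultures and focus remediation among the recommended measures. The summary (1.3) describes the search for metastases and the exclusion of endocarditis as part of adequate treatment. Section 2.3 reports from earlier studies: "Patients seen in consultation by an infectious disease specialist had higher rates of echocardiography". The synopsis states that treating physicians and centers cannot be blinded, and section 10.3.2 that the data are taken from the medical record.

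**The concern.** There are two separate problems.

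The first concerns metastases only. If presence counts, an abscess or endocarditis that existed on the day of the positive culture is an outcome event, although the consult comes later. Whether such a focus is recorded depends on whether anyone looks, and looking is what the consult recommends. An endpoint meant to show fewer complications could then partly show better diagnosis, with the sign reversed.

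The second concerns both endpoints. A 90-day yes/no statement needs 90-day data. Where the specific items end at day 7 or at discharge, a *no* at day 90 may only mean that nobody asked. For sepsis, the 7-day window also opens at the first positive culture, before the consult, so shock present at the outset can be read as progression.

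**Working it through.** **1. Wording side by side**

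| Place | Metastases | Sepsis/septic shock |
|---|---|---|
| Synopsis | development, 90 days | progression, 90 days |
| 3.2 | development, 90 days | progression, 90 days |
| 9.1 | presence or development, 90 days | progression, 90 days |

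The conflict is confined to metastases. Only the 9.1 wording admits foci present at diagnosis.

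**2. Stated window against listed data**

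- Organ dysfunction and septic shock: 7 of 90 days, 7/90 = 7.8% of the stated window.
- Progression of SAB: to discharge.
- Metastases: no dedicated item. The nearest are the infection-focus categories (10.3.2.5), which carry no dates, and the uncomplicated/complicated classification (10.3.2.10).
- Days 30 and 90: readmission with reason and new complaints, by telephone. The addendum on 18-month follow-up describes the same items for these calls.
- Complications are recorded for 90 days (8.3), but 8.2 defines them as events related to the recommended measures, so complications of SAB itself fall outside.

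**3. Order of events for sepsis**

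Under 7.1 the consult follows notification, patient information and faxed consent. The addendum on case recording notes that the registry passes on findings at 24-hour intervals, with telephone or fax as a faster route. The 7-day window therefore includes time before the consult. No onset date and no baseline rule is given.

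**4. Detection of metastases: illustration**

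The protocol gives no metastasis rate and no detection rate, so all rates here are assumptions. The group size follows from section 9.3 and the synopsis: 15 centers × 30 = 450, that is 15 × 15 = 225 per arm. Clustering and period are ignored.

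Let π be the true frequency, equal in both arms, and d the probability that a focus is found. The recorded rate is π × d, so

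observed RR = (π × d_int)/(π × d_ctrl) = d_int/d_ctrl.

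The chance of a significant apparent harm (two-sided 5%) is Φ[(Δ − 1.96·√(2p̄(1−p̄)/n)) / √((p₁(1−p₁)+p₂(1−p₂))/n)]. For π = 0.20 and detection 0.60 vs 0.80, the recorded rates are 0.12 and 0.16 with p̄ = 0.14. This gives (0.04 − 1.96 × 0.0327)/0.0327 = −0.74, and Φ = 0.23.

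| Assumed detection, control vs intervention | Observed RR, no true effect | Chance of significant harm, π from 0.10 to 0.40 | Observed RR if true RR is 0.80 |
|---|---|---|---|
| 0.70 vs 0.80 | 1.14 | 6% to 15% | 0.91 |
| 0.60 vs 0.80 | 1.33 | 13% to 47% | 1.07 |
| 0.50 vs 0.90 | 1.80 | 38% to 97% | 1.44 |

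The last column is 0.80 × d_int/d_ctrl.

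**5. Dilution by foci present at diagnosis**

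With equal detection, let s be the share of control-arm cases already present at diagnosis. Suppose the consult halves new cases (assumed). Then observed RR = s + (1 − s) × 0.50. For s = 0.30, 0.50, 0.70 and 0.90 this is 0.65, 0.75, 0.85 and 0.95.

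**The case against.** Several points limit the concern.

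- A reader might infer that both endpoints count conditions present at diagnosis. The documents do not support this for sepsis, which is worded as progression throughout. What is missing there is a rule for baseline status. SIRS severity and the Pitt score are already collected and could inform one, and the operational detail might sit in an analysis plan. An onset date that is not collected could not be supplied there.
- A reader might infer that sepsis, too, is detected more often with the consult. Nothing shows this. Organ dysfunction and shock rest on routine clinical and laboratory findings; the protocol's evidence on extra work-up concerns echocardiography.
- A reader might infer that a successful consult must raise recorded metastases. That requires the gain in detection to exceed the gain in prevention. With a true RR of 0.80 and detection of 0.70 vs 0.80, the observed RR is 0.91, still a benefit.
- Late events are not wholly lost. Readmission reasons and new complaints could reveal a late spondylodiscitis or endocarditis. This stands, but unspecific telephone questions are a weak basis for a 90-day yes/no endpoint.
- Foci present at diagnosis should balance under randomization and so mainly dilute the effect. This is true of actual foci. It is not true of recorded foci if the arms are examined differently.

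The conflict in wording, the mismatch of windows, and the plausible detection difference for metastases remain.

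**Conclusion.** The concern holds in limited form. The metastasis endpoint has two incompatible wordings, and the 9.1 wording is open to detection bias against the intervention. The direction follows from the protocol's own account of the consult, provided the consult does lead to more work-up. The size cannot be derived from the documents: an RR of 1.14 to 1.80 with no true effect is an illustration over assumed detection rates, not an estimate. Even without any detection difference, counting foci present at diagnosis pulls a real effect towards 1.

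For both endpoints, the specific data listed do not match the stated 90 days. For sepsis, progression cannot be told reliably from baseline status with the items as listed.

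These are secondary endpoints, outside the confirmatory test and without multiplicity adjustment (9.5). The primary 30-day mortality result is unaffected.

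**What to change.** 1. Use one wording, development of new foci, in the synopsis, 3.2 and 9.1.
2. Record the date of each focus and of the onset of sepsis or septic shock. Separate events present at diagnosis from new ones; SIRS severity and Pitt score can support this.
3. Report foci found in the index work-up as a detection measure, together with the proportion having TEE or other imaging by arm. Item 10.3.2.13 is headed by recommended measures, so make explicit that examinations are recorded in control patients too.
4. Either add sepsis/septic shock and metastasis items to the 30- and 90-day forms, or restate both endpoint windows to what is collected.

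The cost is wording, a few CRF items and fewer counted events. Dating does not remove detection bias altogether: a focus missed at first in a control patient and found later would count as new. The imaging proportions should therefore be shown beside the endpoint.
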